## Abstract

In this paper we propose a novel neurostimulation protocol that provides an intervention-based assessment to distinguish the contributions of different motor control networks in the cortico-spinal system. Specifically, we use a combination of non-invasive brain stimulation and neuromuscular stimulation to probe neuromuscular system behavior with targeted impulse-response system identification. In this protocol, we use an in-house developed human-machine interface (HMI) for an isotonic wrist movement task, where the user controls a cursor on-screen. During the task, we generate unique motor evoked potentials based on triggered cortical or spinal level perturbations. Externally applied brain-level perturbations are triggered through TMS to cause wrist flexion/extension during the volitional task. The resultant contraction output and related reflex responses are measured by the HMI. These movements also include neuromodulation in the excitability of the brain-muscle pathway via transcranial direct current stimulation. Colloquially, spinal-level perturbations are triggered through skin-surface neuromuscular stimulation of the wrist muscles. The resultant brain-muscle and spinal-muscle pathways perturbed by the TMS and NMES, respectively, demonstrate temporal and spatial differences as manifested through the human-machine interface. This then provides a template to measure the specific neural outcomes of the movement tasks, and in decoding differences in the contribution of cortical- (long-latency) and spinal-level (short-latency) motor control. This protocol is part of the development of a diagnostic tool that can be used to better understand how interaction between cortical and spinal motor centers changes with learning, or injury such as that experienced following stroke.

## Introduction

Neuromodulation of corticospinal excitability has recently been shown to be an effective tool to increase the efficacy of rehabilitation outcomes (1). For motor control applications, the effects are most often explored as a collective system to identify causal relationships between the brain and muscle, creating a black box-type understanding. In other words, we can relate the inputs (i.e., issued control commands) and outputs of the system (e.g., motor evoked potentials, biomechanics), but the basis of neurophysiological function remain incompletely classified due to the complexities of the corticospinal system. As such, here we present a novel blended neurostimulation protocol that aims to delineate cortical and spinal level processing in specific motor control tasks during volitional wrist motion.

Non-invasive brain stimulation (NIBS) or neuromodulation are ever increasing tools used to improve neuroplastic outcomes in motor neurorehabilitation. Low-cost, safe options such as transcranial direct current stimulation (tDCS) are especially popular due to their ease of use, and economical ubiquity. Generally, tDCS is widely acknowledged as having long-term modulatory aftereffects on cortical excitability that are dependent on dosing (2). For example, repetitive use of tDCS has facilitated improvement in neuroplastic motor relearning (3–8) in multidimensional movement parameters such as peak and accuracy of movement. Generally, applications of tDCS are used under varying assumed mechanisms: (a) depolarize cortical neurons (anodal tDCS) in order to increase cortical excitability; (b) hyperpolarize cortical neurons (cathodal tDCS) to decrease cortical excitability; or (c) as a sham neurostimulation, where the applied voltage/current is low enough to prevent a neural response (9–13). However, the success of tDCS applications is highly variable likely due to inter-individual neuroanatomical differences, the montage, the dosage, as well as unknowns due to gaps in the scientific and functional knowledge related to its application (14–21). Similarly, recent research has shown that tDCS mechanisms can change in effect depending on these variables. For example, the neuroanatomical structures of neurons can cause hyperpolarization at the anode, and depolarization at the cathode (22–24). Ultimately, this can lead to variance in the intended behavior of the applied mechanisms. Largely it is agreed that if the variability can be minimized, significant improvements can be made to tDCS usage and success rate—as such, more robust protocols can be part of the solution to this problem. Success may lead to individualization of tDCS based on baseline inputs by the user.

Another form of NIBS that performs similarly to tDCS is transcranial magnetic stimulation (TMS) (25). TMS is generally considered to have better spatial and temporal resolution (26) in its application. It can be combined with EEG and/or fMRI mappings to optimize stimulation localization. However, tDCS and TMS mechanisms of action are considerably different (27). For example, for TMS, a coil is used to focus a field to induce action potentials compared to tDCS which uses surface electrode pairs to inject an electric field that impacts neuronal activity. Also, TMS is shown to reach deeper neural tissues than those typically affected by tDCS (28). While both can neuromodulate, only TMS can elicit action potentials (29–32). Thus, TMS provides an opportunity for brain level triggering of the motor evoked potential (MEP), while concomitant tDCS provides a tool to precondition a neuromodulated response (33).

These NIBS based modalities are driven primarily at the cortical level to trigger feedforward mechanisms that drive the brain-motor response. However, feedback plays a significant role in not only tuning motor control responses, but also in adjusting motor responses due to dynamic changes, as well as in motor learning (34–36). For example, spinal-level motor control centers are locally responsible for modulating short-latency feedback found at the spinal level. A common way to trigger these spinal-level responses are through the use of neuromuscular electrical stimulation (NMES) (37). In these instances, NMES can activate sensory and/or motor neurons that trigger contraction in a muscle fiber (38, 39). Phasic NMES stimulation shows modulatory effects on spinal-excitability, implying that spinal-driven responses can be modified based on dosing at the local level (i.e., time, frequency). But more significantly, this sensory-motor learning initiated at the muscle-spinal-level can also modulate sensorimotor activity at the cortical level (40, 41). These observations suggest that cortical-level neuromodulation affects downstream spinal responses, while spinal-level neuromodulation affects cortical-level motor learning. There is also a subset of NMES that is called functional electrical stimulation (FES) that operates using a similar concept (i.e., stimulation of a muscle and triggering spinal-level motor control pathways). However, FES is a form of NMES that is applied during a functional task and aids in specific neurorehabilitation for that task-based motion.

A question remains, however, as to how these neurostimulation approaches work together. Recent studies have shown that a combination of NIBS and NMES have beneficial effects in post-stroke and other neurorehabilitation. Specifically, Satow et al. (42) demonstrated that a combined tDCS and NMES protocol improved the outcome in post-stroke gait rehabilitation. This appears to suggest that the neuromodulation provided through tDCS can have a response effect on the spinal-level control, or at least facilitate related motor relearning at the cortical level. These findings were observed by several others (43–45). Schabrun et al. (46) explored the possibility of measuring if these effects had a linear (summative) effect on M1 enhanced excitability but found that the behavior was much more complex. Regardless, Shaheiwola et al. (47) found similar improvements during clinical trials, noting that tDCS enhanced FES when explored through a randomized test. Interestingly, the study subjects had their MEPs measured through TMS at the start and end of the protocol, indicating that those who underwent anodal tDCS during FES showed significant difference from those who underwent FES with a sham tDCS. When exploring individual neurostimulation locations, it was found that cortical level neurostimulation could outperform spinal level applications (48). Similar positive outcomes were measured in TMS effects on NMES (49–51), but in all cases further exploration was suggested as the corticospinal mechanisms behind the outcomes were not fully understood.

In our paper, we propose a novel blended neurostimulation protocol that combines tDCS, TMS, and NMES for the purpose of probing the corticospinal network, and delineating cortico- and spinal-level motor contributions. Here, we will describe our protocol that uses: (a) tDCS to neuromodulate cortical level motor formation and affect motor task urgency and motor response time (4); (b) TMS to elicit a brain-motor perturbation affecting the feedforward motor controller; and (c) NMES to trigger spino-motor perturbations and reflexive motor responses. This multidimensional neurostimulation strategy is part of a larger study that aims to separate corticospinal motor control into functional cortico- and spinal-level blocks, in an effort to build a more patient-specific computational model for clinical applications.

## Materials

### Development of the human-machine interface

The human-machine interface (HMI) was developed in-house using 3D printing, various open-source electronics, and a freely available graphics user interface (GUI) builder for MATLAB. The HMI was designed using CAD software (Fusion 360) and included a handle, armrest, and housing unit (see Figure 1A). Dimensions of the system are: 200 mm × 70 mm × 110 mm (arm rest and housing for electronics), and 143 mm × 25 mm diameter (hand grip). The drafted design was 3D printed using PLA filament with a Robo R2 printer. The handle is connected to the housing unit using a 10 kg Straight Bar Load Cell (TAL220), so that when a user attempts to move the handle a force is measured. The Load Cell data are amplified using a SparkFun Load Cell Amplifier (HX711) and are then sent to an Arduino Mega 2560 R3 (MCU) for data collection and processing. The handle was designed in a such a way so that the wrist rests above the load cell, and the torques produced in the joint correspond to the loading in the sensor.

**Figure 1 fig1:**
[figure not shown]
HMI and protocol set up. **(A)** Hand grip and arm rest are shown in its operational state (left) as well as with the arm rest remove to show the electronics (middle). The electronics—Arduino, amplifier, sensor—and how they are positioned are shown (right). **(B)** An individual seated using the HMI while wearing an EEG cap, EMG and NMES electrodes. **(C)** A depiction of the system setup including posture required for the protocol—red dots indicate EEG/TMS/tDCS electrode placements, while black stripes on arm indicate EMG and NMES electrode placement. **(D)** GUI for the HMI is shown with the welcome screen (top) and task screen (bottom). The task screen shows the target location (blue) as well as the cursor (purple) that moves when the wrist is flexed/extended.

The Arduino MCU is connected to a PC running an open-source MATLAB module known as Psychtoolbox (52, 53). We built a custom GUI (Figure 1D) for this protocol that instructs the user when to relax and when to perform tasks with their non-dominant hand. For example, when the GUI starts, the user is prompted that the test will be in 5 s (relax phase). When the relax phase completes, a target is presented on screen that the user must reach by exerting a force on the HMI hand grip, which is detected by the loadcell. This force is generated by the gripping hand due to the contracting wrist muscles. Thus, these forces generated by the hand via flexion and extension move the cursor in a downward or upward direction, respectively. The cursor sits at the center of the screen when the user applies no force to the HMI and will move away from this zero-point as the applied force increases in either direction. To complete the movement task, the user must keep the cursor on target for 3 s, after which the target is removed from screen and the study participant is asked to relax again for 5 s. When relaxed, the screen cursor goes back to the center of the screen. This procedure is repeated 60 times until completion, the first 20 being wrist flexion movements for random targets on the bottom half of the screen, followed by 20 wrist extension tasks for targets on the top half of the screen and lastly 20 alternating targets. An additional 10 s rest is given after each completed section. The task is performed naturally as per the user’s ability, and periodically under TMS perturbation or NMES perturbation. Specifically, ~25% of the movements are done under neurostimulation in order to perturb the neuromuscular system in random intervals between 2 and 8 repetitions. Sound cues at the beginning of each test create EEG spikes that reflect the beginning of each test. To account for differences between users, an optional calibration step tasks each user with reaching a separate set of targets at higher difficulty than the main test. During this step, data are taken corresponding to HMI control in each direction individually, and are used to determine difficulty and sensitivity to be used in the main program for consistent control from user to user. Calibration can be skipped, and a preset sensitivity can be used, or sensitivity can be manually altered to make the tasks more or less difficult as needed. Time and cursor data are saved after each individual test, and the entire data stream is saved once a whole test session is completed (Figure 2).

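### The fixed 5 s rest and blocked directions make target onset predictable, so any voluntary response time from target onset mixes anticipation with the tDCS effect and with learning

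*Protocol article*

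**What the plan says.** The schedule is in Materials, Development of the human-machine interface.

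- **First rest.** When the interface starts, "the user is prompted that the test will be in 5 s (relax phase".
- **Target onset.** "When the relax phase completes, a target is presented on screen".
- **Later rests.** Once the cursor has been held on target for 3 s, the target disappears and "the study participant is asked to relax again for 5 s".
- **Direction.** The cycle is "repeated 60 times until completion, the first 20 being wrist flexion movements for random targets on the bottom half of the screen". Section 2 consists of 20 extension movements to upper-half targets, and section 3 is described only as "lastly 20 alternating targets".
- **Between sections.** A further 10 s rest follows each completed section.
- **What is random.** Target position is called random in the flexion section. The perturbed movements, about 25% of the total, are spaced at random, 2 to 8 repetitions apart. Nothing random is described for the time of target onset.

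The Introduction gives the role of tDCS as to "affect motor task urgency and motor response time". The interface section says that time and cursor data are saved for each movement. The tDCS protocol section provides sham stimulation as the control. Expected outcomes plans to follow how control changes with motor learning, first in healthy volunteers and later in stroke patients at three or more points of rehabilitation.

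**The concern.** Removal of the target is a visible event that starts a rest of constant length. After a few repetitions a participant can learn when the next target will appear. In the first two sections the participant can also learn which way to move. Random target position prevents planning of the exact force, but not readiness of the correct muscle at the right moment.

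A response time counted from target onset then has two parts: reaction to the target, and anticipation of it. Two comparisons are exposed.

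- **Anodal against sham.** Anticipatory responses that do not depend on tDCS carry no information on its effect and pull the two conditions together.
- **Change with practice.** Anticipation of a fixed rhythm grows with repetition, as motor learning does. Expected outcomes predicts that reliance on sensory input will fall as the task is learned. Earlier, less cue-dependent movement is also what learning a fixed 5 s interval would produce.

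Analysis cannot restore unpredictable onset after the data have been collected.

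**Working it through.** **1. Number of movements.** 20 flexion + 20 extension + 20 alternating = 60, which reproduces the article's total.

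**2. Rest before each target.** Every target follows a 5 s rest except the first of section 2 and the first of section 3, which also follow the between-section rest.
- 5 s rest: 60 − 2 = 58 targets, 58/60 = 96.7%.
- Longer rest: 2 targets, about 5 + 10 = 15 s if the extra 10 s is added to the usual 5 s. This interval is fixed too.

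**3. Direction.**
- Sections 1 and 2: 20 + 20 = 40 of 60, set by block.
- Section 3: if alternating means flexion, extension, flexion and so on, the other 20 are predictable as well, giving 60 of 60. If it means an unpredictable mix, 20 of 60 stay uncertain. The article does not settle which.

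**4. Size of the dilution.** The article gives no rate of anticipation, so this is an illustration on assumed values. Let a share *a* of responses be anticipatory, unaffected by tDCS and equally common under anodal and sham, with the standard deviation unchanged. The contrast shrinks to (1 − *a*) of its value, and the sample needed for the same power rises by 1/(1 − *a*)².

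| Assumed *a* | Contrast kept | Sample multiplier |
|---|---|---|
| 0.10 | 0.90 | 1/0.90² = 1.23 |
| 0.25 | 0.75 | 1/0.75² = 1.78 |
| 0.50 | 0.50 | 1/0.50² = 4.00 |

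**5. Change over time.** Let anticipatory responses be shorter than true reactions by *D* on average. If the share rises from *a*₁ to *a*₂ between visits, mean response time falls by (*a*₂ − *a*₁) × *D* with no change in any pathway. With *a* going from 0.10 to 0.25, again assumed, the fall is 0.15 × *D*. It cancels in an anodal-sham comparison of changes if anticipation grows equally in both. It does not cancel when a person is compared with their own baseline.

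**6. What a variable rest does.** Take an even draw from 3, 4, 5, 6 and 7 s.
- Mean: (3 + 4 + 5 + 6 + 7)/5 = 25/5 = 5 s, as now.
- Chance that the target appears at each second, given that it has not yet appeared: 1/5, 1/4, 1/3, 1/2, 1, that is 20%, 25%, 33%, 50%, 100%.

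Under the present schedule the chance at 5 s is 100% for the 58 targets. Variation reduces predictability but does not abolish it, since a target that has not appeared by 6 s is certain at 7 s.

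**The case against.** The strongest reply is that response time from target onset is not a defined outcome. The timing quantity that feeds Equations 1 to 9 is, by the Figure 2 caption, the offset between stimulation and cursor movement. The NMES protocol section triggers stimulation as the cursor reaches the target, after movement has begun, and perturbed repetitions are spaced at random. Motor evoked potentials are likewise locked to the stimulus. This stands: the fixed rest does not directly affect those measures, and the point is limited to voluntary timing from target onset. It does not remove the point, because the article itself names motor response time as something tDCS should affect and saves the timing of each movement.

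Several stronger readings are tempting, and the document does not support them.

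- **That response times would reflect anticipation instead of reaction.** Anticipation contaminates response times; nothing shows that it replaces them. With the same schedule under sham, it does not by itself create a false tDCS effect.
- **That every onset is announced and every direction known.** The 5 s prompt is explicit only when the interface starts. Strict alternation in section 3 is an inference, and the article does not say that participants are told the order.
- **That a rate of early starts can be calculated.** Any such rate must assume that participants ignore the target and start on their own count, which is the behaviour in question. The article asks them to relax and to perform naturally.
- **That the rest period is spoiled as an EMG or EEG baseline.** The article does not say that it serves as one.
- **That the model's validation rests on response times from this task.** The blended-method section and Study limitations refer to validation in earlier studies.

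It can also be argued that prediction in a repeated task is part of the feedforward learning under study. That is a fair reason to leave the order of directions to the investigators. It is a weaker reason for a constant rest, because learning an interval is not learning to control the wrist.

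**Conclusion.** The concern holds in a limited form. Onset follows a constant 5 s rest for 58 of 60 targets and a longer fixed rest for the other 2. Direction is set by block for at least 40 of 60. Any voluntary response time measured from target onset would therefore mix anticipation with the tDCS effect.

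Between anodal and sham the consequence is mainly loss of sensitivity. Its size depends on a share of anticipatory responses that the document does not give; the multipliers of 1.23 to 4 illustrate assumed shares of 10% to 50%. Across repetitions and visits the consequence is confounding with motor learning, which sham cannot resolve when a person is compared with their own baseline.

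The conclusion assumes that the rest is implemented as written, that anodal and sham sessions share the schedule, and that timing from target onset will be used. It calls for a low-cost improvement to the task and does not put the core impulse-response measures in doubt.

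**What to change.** Draw each rest at random around 5 s with the same mean, for example evenly from 3, 4, 5, 6 and 7 s, and remove the stated length from the on-screen prompt. A balanced list, with each value used 4 times in every section of 20, gives 4 × 25 = 100 s of rest per section, the same as 20 × 5 s now. Record the rest used before each movement, and use the same procedure for anodal and sham sessions and at every visit.

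Optionally, if section 3 is meant to mix the two directions, use a balanced random order of 10 flexion and 10 extension targets, and say in the text what alternating means. This is a design choice; the variable rest does not depend on it.

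The cost is a setting in a custom interface. Mean session length, number of movements and stimulation are unchanged. The change has to be made before data collection.

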
**Figure 2 fig2:**
[figure not shown]
Sample data stream of HMI. Cursor pixel location (black line) is shown during use with corresponding wrist muscle flexion and extension EMGs (blue and red lines, respectively) superimposed. Resulting NMES peaks are shown in measured EMG and a corresponding cursor shift (orange circled area) visible by delayed secondary peak response following stimulation. The time offset between stimulation and cursor movement define the computational properties of the corticospinal controller as described by Equations 1–9. Time is given in seconds—only a portion of the signal is shown to emphasize the sample results.

During experimentation, the HMI is used with Trigno Avanti EMG sensors (Delsys Inc.) (see Figures 1B,C). A standard 10/20 EEG electrode layout is also used to measure cortical activity during motions. Additionally, a standard posture for task performance is used. The participants are seated upright, and the forearm is in mid-prone position with neutral wrist and fingers flexed when the handle is gripped (Figures 1B,C). The participant is instructed to hold the elbow and shoulder angles as close to 90° as well as to remain in that posture throughout the trial. Participants are instructed to also grip the device firmly in a neutral grip. In the event of a posture change, they are promptly asked to bring their posture back to the initial position. Their arm is strapped into the HMI, so it remains centered and flat across the top of the device, and a cloth is placed over the arm/hand so that they cannot visually observe their movements.

Noise can potentially interfere with small magnitude biopotentials, such as EEG, captured in this protocol. To address these, standard filtering methods can be applied to remove known noise sources (60 Hz line noise, motion artifacts, etc.). Additionally, no startling effects are expected due to our ramped up stimulus, so this is not expected to create additional noise.

